## Abstract

**Background:**

The aim of the Youth Depression Alleviation–Combined Treatment (YoDA-C) study is to determine whether antidepressant medication should be started as a first-line treatment for youth depression delivered concurrently with psychotherapy. Doubts about the use of medication have been raised by meta-analyses in which the efficacy and safety of antidepressants in young people have been questioned, and subsequent treatment guidelines for youth depression have provided only qualified support.

**Methods/Design:**

YoDA-C is a double-blind, randomised controlled trial funded by the Australian government’s National Health and Medical Research Council. Participants between the ages of 15 and 25 years with moderate to severe major depressive disorder will be randomised to receive either (1) cognitive behavioural therapy (CBT) and fluoxetine or (2) CBT and placebo. The treatment duration will be 12 weeks, and follow-up will be conducted at 26 weeks. The primary outcome measure is change in the Montgomery-Åsberg Depression Rating Scale (MADRS) after 12 weeks of treatment. The MADRS will be administered at baseline and at weeks 4, 8, 12 and 26. Secondary outcome measures will address additional clinical outcomes, functioning, quality of life and safety.

**Trial registration:**

Australian and New Zealand Clinical Trials Registry ID: ACTRN12612001281886 (registered on 11 December 2012)

## Background

Mental illnesses are the ‘chronic diseases of the young’ [1], and the mental illness that causes most disability in young people is major depressive disorder (MDD) [2]. The peak period for the incidence of depression (or onset of new cases) is from 15 to 29 years of age [3], and about 70% of people will have a subsequent episode of depression after their first episode [4]. Consequently, depression affects a larger proportion of the total life course than any other chronic condition [5]. It causes more impairment (measured in disability-adjusted life-years) than any other illness in high- and middle-income countries, and it is projected to be the major cause of disability internationally in all income groups by 2030 as the burden of infectious disease declines [6]. Youth depression is associated with disruption in development that has effects across the life course, including underachievement in education, underemployment, welfare dependency and diminished number and quality of friendships and intimate relationships [7–9]. The rapid developmental increase in the incidence of depression in adolescence and young adulthood, together with evidence that depression is a neuroprogressive disorder and that effective treatments can be neuroprotective [10], means that establishing effective treatments for this age group is of the utmost importance.

### The effectiveness of antidepressant medications

The effectiveness of antidepressant medications for child and adolescent depression was brought into question by a meta-analysis by Whittington and colleagues [11]. They included both published and unpublished randomised control trials in their meta-analysis and reported that only fluoxetine demonstrated a favourable risk–benefit profile and that sertraline, paroxetine, citalopram and venlafaxine had risk–benefit profiles which were either weak or unfavourable. In a subsequent meta-analysis, Bridge and colleagues [12] reached similar conclusions. They reported a mean effect size of 0.25 (95% CI, 0.16 to 0.34) for antidepressant medications compared with placebo in the treatment of child and adolescent depression, with the fluoxetine trials showing an almost twofold greater effect size of 0.46 (95% CI, 0.29 to 0.62) [12]. In a recent Cochrane review [13], which included trials of all selective serotonin reuptake inhibitors (SSRIs) and newer classes of antidepressants, the authors confirmed that the effects of antidepressant medications for youth depression were small but significant, with rates of remission increasing from 380 per 1,000 for placebo to 448 per 1,000 for medication. It is unclear why fluoxetine appears to be the most effective of the SSRIs in this population, given their similar pharmacodynamics. It might be that fluoxetine’s considerably longer half-life tempers the effects of inconsistent adherence to medication, which can be particularly problematic for young people [14]. Other evidence suggests that the difference is likely to be artefactual. In their recent Cochrane review [13], the authors implemented subgroup analysis to robustly investigate whether the effects of medication were modified by the type of antidepressant. They found no evidence for this hypothesis and concluded that it was premature to assert that fluoxetine is the most effective antidepressant for adolescent depression—especially given that there have been no head-to-head trials.

Concerns about the effectiveness of antidepressants for youth depression have led to a focus on the quality of the trials completed to date. Many of the trials in which investigators have examined antidepressant medication in young people have been industry-sponsored. They have been efficacy trials designed with high degrees of internal validity and have been conducted in highly selected patient populations enrolled in university research centres. They have not been designed to test the effectiveness of the medications in ‘real-world’ clinical populations [15]. Generalising the results from industry-sponsored efficacy trials is problematic and has led to a call for simple clinical trials in real-world patients that will aid practical clinical decision-making [16]. In addition, few studies have investigated treatment effectiveness in young people with depression up to the age of 25. The period from puberty to 25 years of age is continuous in a neurodevelopmental sense, with studies showing that important brain maturational processes start in puberty and continue up to the age of about 25 [17]. As the peak period for the onset of first episodes of depression [3], the period is a key time for effective interventions. Studies that include both children and adolescents—as many of the antidepressant trials do—are likely to confound different developmental pathologies. Childhood-onset depression, which is often a concomitant of an adverse family environment [18], is not a strong predictor of recurrent depression in adulthood [19]. Adolescent-onset depression, in contrast, is continuous with depression that has its onset in young adulthood, with the first depressive episodes in both groups often heralding lifelong recurrent illness [4].

### The safety of antidepressant medications

Additional concerns have been raised about the safety of antidepressants in young people. In 2004, the US Food and Drug Administration (FDA) published the results of a meta-analysis of placebo-controlled trials of antidepressant medications in more than 4,400 children and adolescents. They concluded that the medications doubled the risk of suicidal ideation and behaviour (4% versus 2%) [20]. There were no actual deaths in any of the studies. Subsequent meta-analyses have broadly supported these findings. Bridge and colleagues [12] reported an absolute rate of suicidal behaviour of 3% in those prescribed antidepressant medication, compared with 2% in those who received placebo. They found, however, that the risk difference of 1% was not significant (95% CI, −0.1% to 2%). The authors of the recent Cochrane review found that the rate of suicidal behaviour did increase significantly, from 25 per 1,000 for adolescents treated with placebo to 40 per 1,000 for adolescents treated with antidepressant medication [13]. In response to these increased risks in adolescents, the FDA mandated ‘black box’ warnings for all antidepressants [21], which was followed by similar warnings issued by the Medicines and Healthcare Products Regulatory Agency in the United Kingdom [22], the European Medicines Agency [23] and the Therapeutic Goods Administration in Australia [24]. In 2006, the FDA expanded their warning to include young people up to the age of 25 on the basis of an extended examination of placebo-controlled trials that included almost 100,000 participants in total [20], further emphasising the importance of studies that include patients in this age range.

It is not clear why young people treated with antidepressant medications may be more likely to develop increased suicidality, with hypotheses including that SSRIs induce mixed symptoms in depressed youth with latent bipolarity [25] or that these medicines induce akathisia in a subset of patients [26]. There is some evidence that the small increase in risk can be managed within a supportive clinical framework. The Treatment for Adolescents with Depression Study (TADS), a large trial funded by the US National Institute of Mental Health that included fluoxetine and cognitive behavioural therapy (CBT) (and which is discussed further below), showed that the rate of suicidal behaviour in the group treated with fluoxetine and CBT was half the rate of the group treated with fluoxetine alone during the 12-week trial period [27]. Furthermore, there has been some suggestion that the reported increase in suicidality might not apply to all antidepressants, with the authors of a recent meta-analysis finding no increase in suicidal thoughts or behaviours in young people treated with fluoxetine [28]. The Cochrane review, however, not only confirmed the increase in suicidal thoughts and behaviours associated with antidepressant treatment but also revealed that the type of antidepressant did not modify this risk [13].

Concerns about the efficacy and safety of antidepressant medications for youth depression have led to the development of treatment guidelines that provide only qualified support for their use. The United Kingdom’s National Institute for Clinical Excellence guideline states that psychotherapies should be offered as first-line treatment and that medication should be considered only for moderate to severe depression when there has been insufficient response to psychological therapy [29]. In Australia, the National Health and Medical Research Council guideline also states that psychotherapies should be the first-line treatment, but that fluoxetine should be considered when the patient’s depression is severe, when there has been no response to psychotherapy or when psychotherapy is unavailable [30]. The Australian guideline acknowledges the uncertainty about the use of medications for young people, stating, ‘Many clinically relevant questions remain unanswered by current research evidence, including when a health professional should recommend medication, for whom and at what severity of depression, for how long it should be taken, and how best to monitor progress’ (p 53).

### The effectiveness of psychotherapy and combined treatments

Psychotherapy has proved to be an effective therapy for depression; it is as effective as medication in the short-term treatment of adult patients [27]. Over 80% of published trials of therapy for adolescent depression have studied CBT [31], a manualised, time-limited treatment aimed at improving depressive symptomatology by targeting depressogenic thoughts and related behaviours. Early evidence suggested that CBT was among the most effective treatments for adolescent depression; it showed an effect size approximately twice that of medication [32]. Recent evidence suggests, however, that the effectiveness of psychotherapy for adolescent depression might also be more modest than previously thought, especially in clinical patient groups with severe illness [33].

Evidence derived from studies that have included medication and CBT arms has provided inconsistent support for the effectiveness of one treatment over another or for combined treatment, and it suggests a need for further studies. In TADS [16], the researchers compared four treatments for adolescents with depression: (1) fluoxetine alone, (2) CBT alone (without pill-placebo treatment), (3) combination of fluoxetine and CBT and (4) pill placebo with medical management. The participants were aged from 12 to 17 years and had a mean Clinical Global Impression Scale (CGI) severity score of 4.8, corresponding to ‘markedly ill’ [34]. After 12 weeks of treatment, patients receiving fluoxetine (in the medication-only and combined fluoxetine–CBT treatment arms) showed significantly greater response compared with patients in the CBT and placebo groups, whereas the CBT-alone group did not differ from the placebo group on any measure. The absence of placebo-pill treatment in the group treated with CBT alone, and thus the lack of patient and clinician blinding, was a significant limitation of the study [35], especially given that young people with depression respond particularly robustly to placebo-pill treatment [36]. The benefits of combined treatment versus therapy alone have been examined in other studies, which have produced inconsistent findings. In a study by Melvin and colleagues [37], adolescent participants were allocated to receive sertraline, CBT (also without placebo) or their combination. The study, which was unblinded and had low power to detect differences between treatment groups, did not show any advantage for combined treatment, though CBT alone was more effective than sertraline alone. Mandoki and colleagues [38] observed no difference in depression improvement between participants treated with CBT and venlafaxine compared with CBT and placebo. In a number of small studies, researchers have compared combined treatment with therapy alone for comorbid depression and substance use disorders and have largely found no difference between these treatment approaches [39–42], although Riggs and colleagues [40] observed an improvement in the group treated with CBT and fluoxetine on one depression measure, but not on another (and no difference in substance use outcomes). The authors of a recent Cochrane review [43] found no evidence that combination therapy was more effective than psychological therapy alone for adolescent depression based on clinician-rated remission (OR, 1.82; 95% CI, 0.38 to 8.68).

Overall, the evidence suggests that both CBT and antidepressants are modestly effective for youth depression. The modest effectiveness of both treatments suggest advantages for combined treatment, but this approach currently has limited support. Despite the practical importance of the clinical question, there is still genuine clinical equipoise as to whether first-line management of youth depression should be CBT alone or combined treatment. Although depression is the single greatest cause of morbidity during adolescence and young adulthood, the optimal treatment for the illness in this age group remains a source of considerable uncertainty. With the present protocol, we seek to address this issue by implementing a simple, practical clinical trial in a ‘real-world’ clinical population.

## Methods/Design

### Study design and ethical approval

The study design is a 12-week, parallel-group, double-blind, randomised control trial in which participants with moderate to severe MDD will be allocated to treatment with either CBT and fluoxetine (CBT + FLX) or CBT and placebo (CBT + PBO). The primary hypothesis is that, after 12 weeks of treatment (the trial endpoint), the CBT + FLX group will show greater improvement than the CBT + PBO group in depressive symptoms compared to baseline. The primary outcome measure we will use is the Montgomery-Åsberg Depression Rating Scale (MADRS), an observer-rated depression scale used widely in depression treatment trials because it is both efficient to administer and psychometrically sound [44]. Our secondary hypotheses are that the CBT + FLX group will show greater improvement than the CBT + PBO group on secondary clinical outcomes, functioning, quality of life (QoL) and safety measures at 12 weeks. Assessments will be completed at baseline and at weeks 4, 8 and 12, with follow-up assessment completed by telephone at week 26. All participants will receive manualised CBT, which will be offered weekly to participants for a period of 12 weeks. The study was approved by the Melbourne Health Human Research Ethics Committee (EC00243) in October 2012.

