#### Safety measures

Safety will be assessed using the Suicidal Ideation Questionnaire [53] and the Columbia Suicide Severity Rating Scale [54].

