### Assessment of suicidal ideation and behaviours

Monitoring participants closely for the presence of suicidal thoughts and behaviours is an important component of the study protocol. Participants will be clinically assessed for the presence of suicidal ideation and behaviours at each meeting with their doctor (which will occur at least every 4 weeks) and at their weekly therapy sessions. The assessment will be carried out using a structured tool, the Columbia Suicide Severity Rating Scale [54]. In addition, participants will complete the Suicidal Ideation Questionnaire [53] at the research assessment sessions. If the young person indicates the presence of suicidal thinking in a research assessment, the research assistant will liaise with the participant’s treating doctor or therapist, and the clinician will ensure that an appropriate management plan is in place. If participation in the study interferes with appropriate clinical management of risk of harm to the individual (as adjudged by the treating clinicians), then that person’s participation in the study will be discontinued.

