### Statistical methods and determination of sample size

Primary analyses will be undertaken on an intention-to-treat basis, including all participants as randomised, regardless of treatment actually received. The CBT + FLX group will be compared with the CBT + PBO group using a planned contrast of change from baseline to the week 12 endpoint on the basis of MADRS scores within a mixed-model repeated measures analysis [55]. Stratification variables will be evaluated and retained in analyses where they are measured as significant or quasi-significant. An unconstrained variance–covariance matrix will model within-individual dependencies. Transformation of scores, including categorisation, may be undertaken to meet distributional assumptions and accommodate outliers. Comparisons of changes in MADRS scores from baseline to other time points will be undertaken as secondary analyses.

Models for binary outcomes analogous to the primary analysis approach will be used to compare the remission rates and other dichotomous outcomes between the two treatment arms at endpoints and other occasions of measurement. Relative and absolute risk reduction, number needed to treat [56] and other relevant indices will be calculated for these outcomes. In analyses of scaled secondary variables, methods comparable to those employed in the primary analysis will be used. In exploratory analyses, the effects of moderators and mediators of treatment will be examined. Safety data will be compared between treatment arms—in particular, the rates of suicide-related adverse events—using Fisher’s exact test. All tests will be conducted using a two-sided α level of 0.05 and 95% confidence intervals.

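### The safety hypothesis is worded as greater improvement at week 12, and a mean change in suicidal ideation does not address the emergent suicidality that the protocol describes

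*Protocol article*

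**What the plan says.** All references are to the protocol article.

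- **Study design and ethical approval.** One directional secondary hypothesis covers every secondary domain, safety included: the CBT + FLX group is to show "greater improvement than the CBT + PBO group on secondary clinical outcomes, functioning, quality of life (QoL) and safety measures at 12 weeks". Assessments are at baseline and weeks 4, 8 and 12, with telephone follow-up at week 26.
- **Safety measures.** "Safety will be assessed using the Suicidal Ideation Questionnaire" and the Columbia Suicide Severity Rating Scale.
- **Assessment of suicidal ideation and behaviours.** The two instruments are used in different places. For the self-report scale, "participants will complete the Suicidal Ideation Questionnaire [53] at the research assessment sessions". The Columbia scale belongs to clinical contacts: "Participants will be clinically assessed for the presence of suicidal ideation and behaviours at each meeting with their doctor", at least every 4 weeks, and at weekly therapy sessions.
- **Statistical methods and determination of sample size.** The primary analysis is a contrast of MADRS change from baseline to week 12 in a repeated-measures mixed model. Then: "In analyses of scaled secondary variables, methods comparable to those employed in the primary analysis will be used". A separate sentence has safety data compared between arms, "in particular, the rates of suicide-related adverse events", by Fisher's exact test.
- **The safety of antidepressant medications.** The harm is described as a rate: 4% against 2% in the regulator's meta-analysis, and 40 against 25 per 1,000 in the Cochrane review. One mechanism mentioned is that "these medicines induce akathisia in a subset of patients".

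**The concern.** A safety question asks whether some participants get worse on treatment. The stated hypothesis asks whether the fluoxetine arm improves more, at a single late time point. For a self-report ideation score analysed as a mean, these are different questions.

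Three features of a week-12 mean change work against detecting the harm described. Ideation may fall across the arm because depression lifts, which is an efficacy effect. A small worsening subset is averaged into the rest. Worsening at week 4 or 8 that has settled by week 12 does not enter the week-12 contrast.

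Safety uncertainty is part of the trial's rationale, and the Discussion says that a positive trial would support first-line combined treatment. A favourable mean on a scale listed as a safety measure, under a hypothesis that calls this improvement in safety, could be taken as reassurance that it does not give.

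**Working it through.** **1. Plan's own figures.** No figure is stated for safety. The arm size comes from the sample-size paragraph: effect size 0.35, baseline to week-12 correlation 0.5, total 260. The SD of change is √(2 × (1 − 0.5)) = 1. Power is not stated; at an assumed 80%, n per arm = 2 × (1.960 + 0.842)² / 0.35² = 128.1, so 129 per arm and 258 in total, close to 260. With 1:1 allocation I use 130 per arm.

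**2. How far a worsening subset moves the mean.** The excess is 2 percentage points (4% − 2%, from the Background). The size of worsening is not given; assume 2 SD. The shift against fluoxetine is 0.02 × 2 = 0.04 SD (0.02 to 0.06 SD for worsening of 1 to 3 SD). The standard error of a difference in means is √(2/130) = 0.124 SD, so the signal is about a third of one standard error.

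**3. What a mood benefit does to the contrast.** Let d be the average ideation benefit of fluoxetine in SD units of change. The documents do not give d, so it is varied. The net benefit is d − 0.04. The SD is √((2 + 0.02 × 0.98 × 2²)/2) = 1.019, and SE = 1.019 × 0.124 = 0.126. P(significant for fluoxetine) = Φ(net/SE − 1.96); P(significant against) = Φ(−net/SE − 1.96).

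| d | net | significant for fluoxetine | significant against |
|---|---|---|---|
| 0 | −0.04 | 1% | 5% |
| 0.10 | 0.06 | 7% | 0.7% |
| 0.20 | 0.16 | 24% | under 0.1% |
| 0.35 | 0.31 | 69% | under 0.1% |

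In every row the excess of emergent suicidality is the same.

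**4. The same check, tying d to the MADRS effect.** Assume d = 0.35 × ρ, with ρ an assumed link between mood change and ideation change, and SE = 0.124.

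- Central case (ρ = 0.5, worsening 2 SD): 0.175 − 0.04 = 0.135. Significant benefit Φ(0.135/0.124 − 1.96) = 19%; significant harm 0.1%.
- Low corner (ρ = 0.3, 3 SD): 0.105 − 0.06 = 0.045. Benefit 6%, harm 1%.
- High corner (ρ = 0.7, 1 SD): 0.245 − 0.02 = 0.225. Benefit 44%, harm under 0.1%.

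**5. What the planned event comparison can show.** At 130 per arm, 2% against 4% means 2.6 against 5.2 expected participants. Two-sided Fisher's exact test at 0.05 has about 7% power in the harm direction, and about 4% for 2.5% against 4%. For 2% against 4%, 80% power would need about 1,141 per arm. The approximate 95% CI half-width for the risk difference is 1.96 × √((0.02 × 0.98 + 0.04 × 0.96)/130) = 0.041, or 4.1 percentage points.

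**The case against.** A reader might infer that the mean ideation score will favour fluoxetine whenever the drug relieves depression, or that the hypothesis will usually be confirmed. The documents do not support this. Nothing in them links MADRS change to ideation change, and carrying 0.35 across through a correlation is a modelling assumption. On the figures in step 4 the hypothesis is not confirmed in most trials: 19% centrally, 44% at most.

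A reader might also infer that emergent suicidality goes unexamined. That is wrong too. The statistical section singles out rates of suicide-related adverse events for a between-arm comparison, and the Columbia scale is used at every doctor visit and every week in therapy, so few or early events can be captured.

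Three further points have force:

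- The safety sentence in the statistical section could be read to include the questionnaire, so its assignment to mean change is an inference. But Fisher's test cannot take a scale score without a cut-point, and none is given. The sentence on scaled variables is the one that fits.
- MADRS change at other time points is planned as a secondary analysis, and comparable methods may extend this to ideation at weeks 4 and 8. That would meet part of the timing point. Those contrasts would still be means and would still dilute a subset.
- The section allows categorisation of scores, plans absolute risk reduction for dichotomous outcomes and specifies 95% confidence intervals. The tools for a better analysis are therefore present, but they are not directed at worsening on this scale.

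None of this alters the hypothesis, which is stated in the article and not left to a fuller document. Nor, at about 7% power, would a non-significant event comparison offset an apparent improvement on the scale.

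**Conclusion.** The point holds in a limited form. The safety hypothesis is framed as superiority of improvement at week 12. On the natural reading, the Suicidal Ideation Questionnaire is analysed by a mean change that can favour fluoxetine while a small subset, or participants early in treatment, become more suicidal. That is an efficacy-type result and does not answer the harm set out in the Background.

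The firmest part of the size is the dilution: a 2-point excess worsening by 2 SD shifts the mean by 0.04 SD against a standard error of 0.124 SD. The excess comes from the document; the 2 SD is assumed. The probabilities of a significant benefit (1% to 69% over d from 0 to 0.35; 6% to 44% under the assumed link) are illustrations only. The documents support can favour, not will favour.

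The event analysis and the monitoring stand. What needs correcting is the hypothesis wording and the analysis of one scale.

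**What to change.** 1. **Study design and ethical approval.** Remove safety measures from the greater-improvement hypotheses. State the safety question as a between-arm comparison of emergent suicidality over the whole 12 weeks.
2. **Statistical methods.** Add the proportion with treatment-emergent worsening on the Suicidal Ideation Questionnaire from baseline at any of weeks 4, 8 or 12, with the threshold fixed before unblinding. Report it as a between-arm risk difference with 95% CI.
3. **Adverse events.** Keep the planned Fisher comparison and report it alongside with a 95% CI, so that its low power is visible.
4. **Mean change.** Keep it as a clinical outcome, and say that it is not read as evidence of safety.

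The cost is a change of wording and one extra table from data already collected at the research assessments. The sample size does not change. The downside is that one threshold must be chosen in advance and that a proportion is less precise than a mean.
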